#### Adverse events

We will conduct two group pretest-posttest analyses using 2 multiple regression models. The first model will use logistic regression and the occurrence of one or more adverse events as the outcome variable (0 if patient experiences no adverse events, 1 if the patient experiences ≥1). The model will compare the change in the percentage of patients experiencing one or more adverse events from baseline to post-implementation in Phase I Implementation units to the change in Phase II Implementation units across 2 baseline periods. The model will use an interaction term defined as unit type (Phase I vs. Phase II) multiplied by the intervention period (year 1 vs. year 2) to examine the change in the outcome. (i.e., difference-in-differences analysis). We will use standard errors robust to the clustering of patients within each hospital. The second model will use Poisson regression and the number of adverse events per 1000 discharges as the outcome variable. This method accounts for episodes in which a patient may experience more than one adverse event. This model will compare the change in the number of adverse events per 1000 discharges from baseline to post-implementation in Phase I Implementation units to the change in Phase II Implementation units across 2 baseline periods. The model will use an interaction term similar to that described above (i.e., difference-in-differences analysis) and include standard errors robust to the clustering of patients within each hospital. Covariates for both models will include patient age, sex, race, payer, admission source, primary diagnosis, Elixhauser index [45], type of admission (i.e., observation vs. inpatient), and discharge destination (i.e., home vs. other).

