### Study sites

In collaboration with the Society of Hospital Medicine (SHM) and the American Nurses Association (ANA), we issued a national call for applications for the RESET project. We received 14 applications from hospitals throughout the U.S, each of which was independently assessed by two members of research team for need (i.e., similar interventions had not already been implemented), commitment, and potential for success. Four hospital sites were selected, with two hospitals in the Southeast U.S., one in the Midwest, and one in the West. All hospitals are nonprofit and have between 200 and 350 beds. Two are non-teaching hospitals and two are teaching hospitals, though neither is a major affiliate of a medical school.

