#### Exploration and preparation

Exploration began with solicitation of potential sites, review of site applications, and selection of final study sites. Mentors were matched with sites and began coaching to assist site leaders in engaging stakeholders and selecting specific adaptations of interventions to meet their needs. We prepared and distributed a 52 page RESET Implementation Guide to site leaders, which includes detailed descriptions of each AIMS intervention, recommended strategies for successful implementation, milestones, and tools (e.g., an example project charter, work plan and communication plan templates, roles and expectations of unit co-leaders, and example structured communication tools to be used in Enhanced Interprofessional Rounds).

During Preparation, mentors assisted site leaders as they conducted a formal evaluation of organizational capacity for planned interventions and created an implementation plan. In collaboration with site leaders, we administered the Organizational Readiness for Implementing Change (ORIC) survey to all professionals on the study units [34]. ORIC is a 12 item instrument based on Weiner’s theory of organizational readiness for change and measures two core constructs: change commitment and change efficacy [35] ORIC is ideal for our study because it is brief, reliable, and items are understood by frontline hospital based professionals [34]. The ORIC results were shared with site leaders and mentors led discussions reviewing the results during monthly calls.

In preparing the implementation plan, site leaders selected 1 unit ideally suited for initial implementation of interventions (Phase I Implementation) and 1–2 units for later implementation of interventions (Phase II Implementation). Implementation of the AIMS interventions on the Phase I units was planned to occur in or around October 2018 and implementation on the Phase II units is to occur in or around October 2019. Outcome data are collected for both Phase I and Phase II units before and after implementation of the AIMS interventions on the Phase I units (See Figure 2).

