#### Teamwork climate

First, we will compare baseline teamwork climate scores to post-implementation scores for Phase I Implementation Units. We will use two-sample t tests (for all professionals) and paired t tests (for professionals responding to both surveys). Data is expected to be normally distributed based on prior studies [36, 39]. Second, we will compare baseline teamwork climate scores to post-implementation scores for Phase II Implementation Units using two-sample t tests (for all professionals) and paired t tests (for professionals responding to both surveys). Third, we will conduct a two group pretest-posttest analysis using multiple linear regression with teamwork score as the outcome variable. The model will compare the change in teamwork climate from baseline to post-implementation in Phase I Implementation units to the change in Phase II Implementation units across 2 baseline periods. The model will use an interaction term defined as unit type (Phase I vs. Phase II) multiplied by the intervention period (year 1 vs. year 2) to examine the change in teamwork climate (i.e., difference-in-differences analysis). We will use standard errors robust to the clustering of professionals within each hospital.

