### Power and sample size

#### Teamwork climate

Prior research using similar interventions has shown that teamwork climate increases for all professionals, but the improvement is greatest for nurses [36, 39, 40]. Therefore, we estimated a target sample size of nurses using results from prior studies. A sample size of 68 achieves 90% power to detect a mean of paired differences of 4.0 with an estimated standard deviation of differences of 10.0 and with a significance level of 0.05 using a two-sided paired t-test [46]. This sample size reflects completed paired surveys for 17 nurses at each site and is extremely feasible based on prior studies [36, 39, 40].

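### The three difference-in-differences regressions use hospital-clustered standard errors with only four hospitals, so their error rate depends on a small-cluster method that the plan does not fix

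*Protocol article*

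**What the plan says.** The article fixes three things that bear on this point.

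- **Number of clusters.** Study sites: "Four hospital sites were selected, with two hospitals in the Southeast U.S., one in the Midwest, and one in the West".
- **Variance estimator and cluster level.** Statistical analyses, Teamwork climate, for the linear model: "We will use standard errors robust to the clustering of professionals within each hospital". Statistical analyses, Adverse events, for the logistic model: "We will use standard errors robust to the clustering of patients within each hospital". The Poisson model is likewise to "include standard errors robust to the clustering of patients within each hospital".
- **Layout within hospitals.** Exploration and preparation: "site leaders selected 1 unit ideally suited for initial implementation of interventions (Phase I Implementation) and 1–2 units for later implementation of interventions". Each hospital therefore supplies both unit types, and the tested term in all three models is the interaction of unit type with period.

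No reference distribution, degrees of freedom or finite-cluster scaling is named. A 5% level appears only in the teamwork sample size ("with a significance level of 0.05 using a two-sided paired t-test"); I assume the same level for adverse events. The teamwork section also lists two-sample and paired t tests, which carry no cluster adjustment and are outside this point.

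**The concern.** The sandwich variance is justified as the number of clusters grows. The number of patients or nurses inside each cluster does not help. With four hospitals it is estimated from four cluster totals. It is then imprecise and, without scaling, biased downwards. Comparing the resulting statistic with a normal critical value treats that estimate as if it were known.

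The article rests its claim to a rigorous evaluation, with historic and concurrent controls, on the difference-in-differences comparison. If the normal reference is used, a false claim of benefit becomes about three to four times as likely as the nominal rate. If a valid reference is used instead, the price is paid in power, and the stated 90% for adverse events does not show it.

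**Working it through.** **The plan's own figures.** Teamwork: 17 × 4 = 68 pairs, difference 4.0, SD 10.0, two-sided 0.05. The noncentrality is 4/(10/√68) = 3.30 and the power is 90.2%, so the stated 90% reproduces. That calculation is for a paired t test and does not involve the clustered models. Adverse events: the formula behind 1936 patients per year cannot be identified. An unclustered two-period Poisson comparison of 0.0893 × 0.96 = 0.0857 with 0.0857 × 0.67 = 0.0574 gives 1880 (score) or 1905 (log) per year, which is close.

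**Error rate, balanced case.** Inputs: G = 4 hospitals, both unit types in each, two periods.

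1. With equal cells the interaction estimate is, to first order, the mean of four within-hospital differences-in-differences d₁ to d₄.
2. The uncorrected sandwich variance is Σ(d − d̄)²/G². Multiplying by G/(G−1) = 4/3 gives s²/4, the ordinary squared standard error of a mean of four values.
3. If the four values are roughly normal with equal variance, the scaled statistic follows t(3), and the uncorrected statistic follows √(4/3) × t(3).
4. Rejection rates under a true null:

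| Standard error | Reference | Calculation | Rate |
|---|---|---|---|
| Scaled | Normal, 1.96 | P(\|t₃\| > 1.96) | 14.5% |
| Uncorrected | Normal, 1.96 | P(\|t₃\| > 1.96 × √(3/4) = 1.70) | 18.8% |
| Scaled | t(3), 3.18 | P(\|t₃\| > 3.18) | 5.0% |
| Uncorrected | t(3), 3.18 | P(\|t₃\| > 3.18 × √(3/4) = 2.76) | 7.0% |

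These rates need no assumed intracluster correlation.

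**Simulation check.** Linear, logistic and Poisson models were simulated under a true null, with 1000 to 2500 runs per scenario. Assumed: hospital SD 0.3 and unit-by-period SD 0 to 0.2 on the model scale, 0 to 8 covariates, equal and unequal unit sizes.

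- Normal reference: 14–19% scaled and 18–24% uncorrected. The highest values came from unequal units.
- t(3) reference: 4–8% scaled and 6–11% uncorrected.

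**What a valid reference does to power.** Assumed: 1936 patients per year split evenly between unit types (968 each), baseline rate 0.0893, a 4% yearly decline, rate ratio 0.67 for the interaction, and no excess variation between units.

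- Expected events: 968 × 0.0893 = 86.4 in each baseline cell, 86.4 × 0.96 = 83.0 in the later Phase II cell, and 83.0 × 0.67 = 55.6 in the later Phase I cell.
- SE of the log ratio: √(1/86.4 + 1/86.4 + 1/83.0 + 1/55.6) = 0.231.
- Noncentrality: −ln(0.67)/0.231 = 0.400/0.231 = 1.74.
- Power: about 41% with 1.96 and a known SE, and about 23% with t(3), against the stated 90%.

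**The case against.** The strongest reply is that the inflation is conditional. The article names no reference distribution, and the same four-cluster variance with scaling and t(3) holds its level. This stands, and it limits the conclusion. A reader might infer that every primary p-value in the trial carries a 15–20% false-positive rate. The document does not support that, for three reasons:

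- The rate needs normal critical values. These are usual for logistic and Poisson Wald tests, but the article does not state them.
- The teamwork model is a linear regression, where a t reference is ordinary practice. It is affected only if its software does not use t(G−1).
- The teamwork t tests use no clustered standard error, so only the three regressions are in question.

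A second reply is that degrees of freedom belong in an analysis plan that is not shown. This stands in part. A missing technical detail would be no finding here. But the article does fix the estimator, the cluster level and the number of clusters, and that combination cannot be relied on without a correction.

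A reader might also infer that the models wrongly leave out hospital or unit effects. The article lists patient covariates for the adverse-event models and none for teamwork, and excludes site terms in neither. In the balanced case additive hospital effects largely cancel from the interaction, so they do not drive the error rates above.

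**Conclusion.** The concern holds in conditional form for the three difference-in-differences regressions. With normal critical values, a nominal 5% test has a true level of 14.5% (scaled) to about 19% (uncorrected) in the balanced case, and somewhat more with unequal units. With t(3) the level is about 5% (scaled) or 7% (uncorrected). The article leaves open which of these applies; the normal reference is the likelier default for the two adverse-event models.

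The balanced-case rates rest on the four hospital-level contrasts being roughly normal with equal variance. The simulated ranges depend on the assumed variance components and unit sizes. The power figures of 41% and 23% depend on the even split between unit types, which the article does not give, and on there being no extra variation between units.

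**What to change.** In Statistical analyses, Teamwork climate and Adverse events, replace the plain hospital-clustered standard errors in the three regressions with one named small-cluster method, chosen before the outcome data are analysed:

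- bias-reduced (CR2) standard errors with Satterthwaite degrees of freedom; or
- one within-hospital difference-in-differences per site, with the four values tested on t(3).

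The two agree only in the balanced, unadjusted case, so the plan should say which is primary. Hospital or unit fixed effects may be added, but they do not cure the four-cluster problem.

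In Power and sample size, Adverse events, restate the power for the interaction on the same reference distribution, and give the assumed split of patients between unit types.

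The change needs only analysis wording and a software option, with no new data. The cost is in precision. For the same standard error, moving from 1.96 to 3.18 widens a confidence interval by a factor of 3.18/1.96 = 1.62, and the restated power will be below 90%.

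### The difference-in-differences models name no hospital or unit term, so a change in hospital mix between years would enter the interaction as avoidable error

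*Protocol article*

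**What the plan says.** Protocol article, Study sites: "Four hospital sites were selected". Under Exploration and preparation, "site leaders selected 1 unit ideally suited for initial implementation of interventions (Phase I Implementation) and 1–2 units for later implementation". Both unit types are therefore present in every hospital, with 8 to 12 units in all.

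Statistical analyses, Teamwork climate: the two-group analysis is a "multiple linear regression with teamwork score as the outcome variable", built on a unit type by year interaction. No covariates are named. Hospital is handled by one sentence: "We will use standard errors robust to the clustering of professionals within each hospital".

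Statistical analyses, Adverse events: the logistic model uses "unit type (Phase I vs. Phase II) multiplied by the intervention period (year 1 vs. year 2"), and the Poisson model uses a similar term. The covariates are patient and admission variables: "Covariates for both models will include patient age, sex, race, payer, admission source, primary diagnosis, Elixhauser index", then admission type and discharge destination. Hospital again appears only in the error structure: "We will use standard errors robust to the clustering of patients within each hospital".

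Power and sample size: the adverse-event target is 482 patients per site per year. No split between Phase I and Phase II units within a site is given. The planned teamwork effect is 4.0 points.

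**The concern.** The layout pairs the two unit types within each hospital, so the natural comparison sets each hospital's Phase I unit against that hospital's own Phase II units. The stated models pool across hospitals instead. A clustered standard error changes the stated uncertainty, not the estimate. The pooled interaction is a contrast of four cell averages, each weighted by whichever hospitals supplied the respondents or charts. If those weights move between year 1 and year 2 within a unit type, part of the estimated effect reflects which hospitals responded, not what the intervention did.

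Such movement is foreseeable. The teamwork survey depends on response, and the all-professional regression has no per-site quota. For adverse events the site total is fixed, but the Phase I/Phase II split within a site is not. Both primary outcomes are affected.

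**Working it through.** **Inputs from the document.** Four hospitals; one Phase I unit and one or two Phase II units in each; interaction of unit type with year; planned teamwork effect 4.0; expected adverse-event reduction 33%; background decline about 4% a year. The plan gives no figure for hospital mix or between-hospital spread, so there is nothing of its own to reproduce on this point. The 4.0 serves only as a yardstick. It comes from the paired calculation for nurses (68 pairs, SD of differences 10.0, power recomputed as 0.902), not from the regression.

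**Assumptions, not in the document.** Between-hospital SD of 3 to 8 points for teamwork, or 0.2 to 0.4 on the log rate for adverse events; residual SD of 10 or 14 points; cell counts as shown.

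**Step 1: what leaks.** Let a_h be the level of hospital h and w_h its share of a cell. Without hospital terms, the linear interaction equals the true effect plus

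Σ a_h [(w_h, Phase I year 2 − w_h, Phase I year 1) − (w_h, Phase II year 2 − w_h, Phase II year 1)].

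If each unit type keeps its mix over the two years, both brackets are zero and nothing leaks, even if the mixes of the two unit types differ. Fits to expected values confirm this: teamwork 4.00 and Poisson log rate ratio −0.360, with and without hospital terms. The logistic estimate with equal cells moves only from −0.360 to −0.356, through non-collapsibility.

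**Step 2: a worked shift.** Take four equally spaced hospital levels with SD 3: ±4.02 and ±1.34. In Phase I year 2 only, let the counts be 0.8, 0.9, 1.1 and 1.2 times their year 1 values. The shares change by −0.05, −0.025, +0.025 and +0.05.
- Teamwork leak = 2 × (0.05 × 4.02 + 0.025 × 1.34) = 0.47, so a true 4.0 reads about 4.5. At SD 6 it reads 4.9.
- With multipliers 0.5, 0.75, 1.25 and 1.5 the leak is 2.5 times as large, and a true 4.0 reads 5.2 (SD 3) or 6.3 (SD 6).
- Poisson, log-rate SD 0.2, smaller shift: the mean hospital multiplier goes from 1.020 to 1.052. The log rate ratio is ln(0.67/0.96) + ln(1.052/1.020) = −0.360 + 0.031 = −0.329, a rate ratio of 0.72 against a true 0.70. At SD 0.4 it is −0.301 (0.74). The larger shift gives 0.75 to 0.80.

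With hospital indicators every case returns the true value. These shifts line up with hospital level and so show an unfavourable direction; the opposite alignment reverses the sign.

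**Step 3: typical size for teamwork.** If each of the 16 cell counts (4 hospitals × 2 unit types × 2 years) varies independently with coefficient of variation c, and hospital levels have SD σ, then approximately

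SD of leak = σ × c × √(4 × 3/16) = 0.866 σc.

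| Cell counts | c | σ = 3 | σ = 5 | σ = 8 |
|---|---|---|---|---|
| drift uniformly within ±10% | 0.2/√12 = 0.058 | 0.15 | 0.25 | 0.40 |
| drift uniformly within ±20% | 0.4/√12 = 0.115 | 0.30 | 0.50 | 0.80 |
| vary freely, 12 to 22 | √10/17 = 0.186 | 0.48 | 0.81 | 1.29 |
| vary freely, 8 to 26 | √30/17 = 0.322 | 0.84 | 1.40 | 2.23 |

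Simulation agrees, with slightly larger values in the last row (about 0.86, 1.44 and 2.3). The mean leak is zero throughout.

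**Step 4: precision.** With equal cells (20 respondents each, residual SD 10) the SD of the estimate is the same either way: √(4 × 100/80) = 2.24 by formula, 2.26 simulated. Under varying mix, the SD without hospital terms is 2 to 13% larger for teamwork and about 0.5 to 6% larger for Poisson. In the widest case (8 to 26, residual SD 14) hospital terms reduce the SD from 3.68 to 3.44 (σ = 5) and from 4.10 to 3.43 (σ = 8).

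**The case against.** The strongest reply is that this is a condensed article: the covariates are introduced with the word include, the teamwork model lists none, and site indicators may appear in a fuller plan. That is possible. But the article does state how hospital is handled in each analysis, through the standard errors, and gives a detailed covariate list for adverse events without hospital in it. The point concerns that stated choice.

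The remaining objections narrow the point, and they stand:
- A reader might infer that any imbalance leaks, for instance because some sites have one Phase II unit and others two. Units were chosen during Preparation, and a mix that stays fixed over the two years cancels in the linear and Poisson models.
- A reader might infer systematic bias. The document gives no reason for the mix to shift in step with hospital level; the error is random in sign and averages zero.
- A reader might infer a general loss of precision. There is none with equal cells.
- Errors of 0.8 points and more at σ = 5 require counts redrawn independently each year, so that one cell could go from 8 to 26. The survey goes each year to all listed professionals on the study units, with up to five reminders, so smaller drifts are also plausible.
- The paired t-tests that underlie the teamwork sample size are unaffected, because hospital level cancels within a person.

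**Conclusion.** The point holds in limited form. The stated models leave the interaction open to changes in hospital mix between years within a unit type, although the paired layout would allow this to be removed. Teamwork is the more exposed outcome, with no per-site quota for the regression and no stated covariates. For adverse events the constant site target limits shifts in the overall mix, but not in the split between unit types.

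The actual size cannot be derived from the document. On the stated assumptions, the teamwork error SD runs from zero (stable mix), through 0.15 to 0.8 points (10 to 20% drift), to about 2.3 points (the widest free variation with σ = 8), against a yardstick of 4.0. This is a free improvement, not a flaw that invalidates the design. It is separate from the weakness of clustered standard errors with only four clusters, which hospital terms do not cure.

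**What to change.** State that the teamwork, logistic and Poisson difference-in-differences models include hospital fixed effects, or preferably unit fixed effects, which also absorb level differences between units of the same hospital. Hospital indicators add three parameters per model. Unit indicators replace the unit-type main effect by 7 to 11 indicators (8 to 12 units), and the interaction remains estimable. Add one sensitivity analysis with hospital-by-year effects, so that each hospital's Phase II units act as its own concurrent control; this adds three more parameters to a model with hospital effects. Keep the clustered standard errors, and treat their small-sample adequacy as a separate matter. Report respondents and charts by hospital, unit type and year, so that any shift in mix can be seen.

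The cost is a sentence or two of analysis wording and a few parameters, with no new data. The logistic coefficient becomes conditional on hospital, a change of about 0.004 on the log-odds scale in the equal-cell example.

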#### Adverse events (primary outcome)

We use the Medicare Patient Safety Monitoring System (MPSMS) methodology to detect adverse events. MPSMS is a medical record-based national patient safety surveillance system that provides rates for specific inpatient adverse event measures [41, 42]. MPSMS data have been used in Agency for Healthcare Research and Quality National Health Care Quality and Disparities Reports and currently serve as the major national-level patient safety data source for the U.S. Department of Health and Human Services [1]. MPSPS has been shown be reliable and valid in detecting adverse events among hospitalized patients [41, 43]. We collect data for 9 types of adverse events which commonly occur among hospitalized general medical patients, including adverse drug events, hospital acquired infections, pressure ulcers, and falls. Data will be reported as the number and percentage of patients experiencing one or more adverse event and the number of adverse events per 1000 discharges.

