#### Efficiency measures (secondary outcomes)

We assess efficiency of care using hospital length of stay (LOS) and 30-day readmissions. LOS will be reported as median (IQR) as data are typically skewed in distribution. As for patient experience data, the research nurse will obtain data on a yearly basis for patients admitted to study units, excluding those transferred from other hospitals and those initially admitted to other units. Research nurses will de-identify data prior to importing it into REDcap. This data will include information on patient age, sex, race, payer, admission source, primary diagnosis, secondary diagnoses, type of admission (i.e., observation vs. inpatient), and discharge destination (i.e., home vs. other).

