#### Adverse events

We used data from the AHRQ National Scorecard on Rates of Hospital Acquired Conditions 2010 to 2015, which also uses the MPSMS methodology, to estimate current rates for the adverse events included in our study [47]. The national rate for adverse events included in our study is 89.3 per 1000 discharges. Based on prior studies, we conservatively expect a 33% reduction in the rate of adverse events as a result of our interventions [36, 48]. Importantly, adverse events have recently declined by approximately 4% each year [47]. Accounting for this trend, we estimate a need to enroll a target sample size of 1936 patients each year (482 per site per year) to have 90% power to detect a significant improvement in adverse events using a Poisson regression accounting for clustering of hospitals (r = 0.3).

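### Both adverse-event models adjust for discharge destination, which is settled after the intervention and after the events, so the primary effect estimate is liable to bias

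*Protocol article*

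**What the plan says.** The section on statistical analyses of adverse events specifies two regression models. Its covariate sentence applies to both: "Covariates for both models will include patient age, sex, race, payer, admission source, primary diagnosis, Elixhauser index", followed by "type of admission (i.e., observation vs. inpatient), and discharge destination (i.e., home vs. other". The effect of interest is an "interaction term defined as unit type (Phase I vs. Phase II) multiplied by the intervention period (year 1 vs. year 2" comparison, that is, a difference-in-differences estimate.

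Adverse events are one of the two primary outcomes. The outcome section describes nine event types among hospitalized patients, including "adverse drug events, hospital acquired infections, pressure ulcers, and falls".

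The article gives no reason for including destination and describes no adverse-event analysis without it.

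**The concern.** A covariate helps in this analysis if it describes how patients differed before exposure. Destination describes how the stay ended. A fall, a pressure ulcer or an infection can make discharge somewhere other than home more likely. A programme of bedside interprofessional rounds, physician localization and patient engagement could also change discharge planning directly. If both happen, destination is a common effect of intervention and outcome. Comparing patients within levels of it then creates an association between the two that is not the intervention effect. The difference-in-differences structure does not remove this, because the direct effect on destination would appear only in Phase I units after implementation.

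The estimate of a primary outcome is at stake. A real benefit could be understated or overstated, and a null effect could look like harm or benefit. Nothing in the fitted model would reveal it.

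**Working it through.** **Inputs from the article (power section for adverse events).** "The national rate for adverse events included in our study is 89.3 per 1000 discharges"; "we conservatively expect a 33% reduction in the rate of adverse events as a result of our interventions", so a rate ratio of 0.67; a background decline of about 4% a year; 1936 patients a year for 90% power.

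**Inputs assumed, because the article gives none.** Share not discharged home among event-free patients, 25% to 40%. Odds ratio of an adverse event on non-home discharge, 2 to 3 (5 as an extreme). Odds ratio of the intervention's own effect on non-home discharge, 0.8 to 0.67 (1 means no direct effect). Two-sided alpha 0.05, as in the teamwork calculation.

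**1. The plan's own figure.** Simple two-group Poisson formula, with l1 = 0.0893 × 0.96 = 0.0857 and l2 = 0.67 × 0.0857 = 0.0574:

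n = (1.960 + 1.282)² × (1/0.0857 + 1/0.0574) / (ln 0.67)² = 10.51 × 29.07 / 0.1604 ≈ 1905

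This is within 2% of 1936. Other formulas also come close, so the method actually used cannot be identified. The match does confirm the rate, trend and effect as inputs.

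**2. True effect without destination.** The rate ratio is 0.670. The odds ratio is [0.0574/0.9426] / [0.0857/0.9143] = 0.650.

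**3. Logistic model with destination.** Let T be the intervention, Y an adverse event and D non-home discharge. Within a level of D,

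adjusted OR = OR × [P(D|T1,Y1) × P(D|T0,Y0)] / [P(D|T1,Y0) × P(D|T0,Y1)]

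When the effects on D are multiplicative on the odds scale, the factor is the same for home and non-home discharge.

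- *Mild case* (25% non-home, event OR 2, intervention OR 0.8). The four probabilities are 0.348, 0.250, 0.211 and 0.400. Factor (0.348 × 0.250)/(0.211 × 0.400) = 1.03; 0.650 becomes 0.67.
- *Stronger case* (40% non-home, event OR 3, intervention OR 0.67). The probabilities are 0.573, 0.400, 0.309 and 0.667. Factor (0.573 × 0.400)/(0.309 × 0.667) = 1.11; 0.650 becomes 0.72.
- *No direct effect* (intervention OR 1). The factor is exactly 1, so 0.650 does not change.
- *Opposite sign* (25% non-home, event OR 2, intervention OR 1.25). The probabilities are 0.455, 0.250, 0.294 and 0.400. Factor 0.966; 0.650 becomes 0.63, which overstates the benefit.

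**4. Poisson model with destination.** Large-sample fits of the interaction model to the expected cell proportions, with at most one event per patient:

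| Event OR on D | Intervention OR on D | True 0.67 becomes |
|---|---|---|
| 2 to 5 | 1 | 0.672 to 0.682 |
| 2 | 0.8 to 0.67 | 0.692 to 0.715 |
| 3 | 0.8 to 0.67 | 0.709 to 0.744 |
| 5 (extreme) | 0.67 | 0.775 to 0.779 |

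At event OR 2 to 3, the loss of log effect runs from 1 − ln 0.692/ln 0.67 = 8% to 1 − ln 0.744/ln 0.67 = 26%.

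**5. True null.** With no direct effect on destination, both models return 1.00. With event OR 2 to 3 and intervention OR 0.8 to 0.67, they return about 1.03 to 1.11.

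**6. Against sampling error.** Assume 1936 patients a year split equally, so 968 per unit type and year. Expected events are 86.4, 86.4, 83.0 and 55.6. The standard error of the log difference-in-differences ratio is √(1/86.4 + 1/86.4 + 1/83.0 + 1/55.6) = 0.23 before clustering. The Poisson shifts, ln(0.692/0.670) = 0.032 to ln(0.744/0.670) = 0.105, are 0.14 to 0.45 of one standard error.

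**7. Power on the simple scale of step 1.** With 1936 per group, power is about 90% at 0.67, 85% at 0.696 and 70% at 0.744. That formula ignores the interaction and clustering, so these figures show only the relative loss.

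**The case against.** **The consequence is conditional.** A reader might infer that the estimate is biased simply because adverse events influence destination. The calculation does not support that: with no separate intervention effect on destination, the logistic odds ratio does not move and the Poisson ratio hardly does. The article names no such effect. Its stated outcomes are teamwork, adverse events, patient experience, length of stay and readmission. This objection stands. The route is plausible for a redesign of care delivery, but it is assumed.

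**The shift is small against sampling error.** At less than half a standard error it would not by itself invalidate the trial. That also stands and limits the severity. It does not justify keeping a covariate that can add a systematic error.

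**Destination may stand in for frailty.** Age, the Elixhauser index and admission source already cover part of this. A check added an unmeasured frailty (0.5 on the log-odds scale per standard deviation for both events and destination, 30% non-home). The unadjusted rate ratio was 0.677 and the destination-adjusted one 0.71 to 0.76 for the same odds ratios. Frailty was equally distributed across unit types and years in that check. It therefore does not exclude some gain from adjustment if frailty changed differently between them.

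**Tempting extensions that the article does not support.**
- One could extend the criticism to observation versus inpatient status, but the article does not say that this is the final status rather than the status at admission.
- One could extend it to the Elixhauser index, but the article does not say that the index includes diagnoses arising in hospital. Such coding detail is commonly left to the analysis plan.
- The efficiency-measures section also lists destination, but only among data to be obtained ("primary diagnosis, secondary diagnoses, type of admission (i.e., observation vs. inpatient), and discharge destination (i.e., home vs. other"). Collecting it is not an error.

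**Conclusion.** The point holds as a risk of bias. The article fixes, in both primary adverse-event models, a covariate determined after exposure and after the outcome events, with no rationale and no analysis without it.

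If the redesign also lowers non-home discharge directly, a planned rate ratio of 0.67 would be estimated at about 0.69 to 0.74, and a null at about 1.03 to 1.11, under the assumed odds ratios. If it raises non-home discharge, the bias runs the other way. If destination responds to events alone, the effect is negligible. All destination inputs are assumptions, so neither size nor sign can be claimed from the article.

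This should be fixed before analysis. It does not invalidate the design, and the sample size is unaffected.

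**What to change.** Delete discharge destination from the covariate list of both primary adverse-event models. Keep the other listed covariates, including primary diagnosis. If the team wants a destination-adjusted result, report it as a labelled sensitivity analysis and state that the covariate is measured after the outcome.

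The cost is one line of analysis wording. No new data are needed. The possible downside is a small loss of adjustment for frailty, which the remaining covariates partly cover.
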